### Primary outcome measures

#### Work ability

Work ability is measured with the Work Ability Index [4]. This widely used index measures self-assessed work ability and consists of seven items. For the purpose of this study, only three of the seven items were considered relevant and are thus measured. These three items are 1) perceived work ability in general, 2) perceived work ability in relation to physical demands and 3) perceived work ability in relation to mental demands. Different studies have shown that the validity and reliability of Work Ability Index are acceptable to good [23,24].

#### Health-related quality of life

In this study, health-related quality of life is measured with the SF-12 [25,26]. The SF-12 includes items referring to mental health as well as physical health. The following eight dimensions are included: physical functioning, role limitations due to physical problems, bodily pain, general health perceptions, vitality, social functioning, role limitations due to emotional problems, and mental health [27]. Different studies have shown that the validity and reliability of the SF-12 are adequate [26,27].

### Secondary outcome measures

#### Need for recovery

Need for recovery is measured with an existing Dutch questionnaire on the Experience and Evaluation of Work (Dutch abbreviation: VBBA) [28,29], which has shown to be valid and reliable (0.86) [30,31]. The scale consists of eleven dichotomous items (yes/no), representing short-term effects of a working day.

#### Physical workload and musculoskeletal symptoms

Questions about the physical workload are based on questions used for the Periodical Health Screenings survey in the construction industry. In the Netherlands, this survey is widely used and common among construction workers who participate in the Periodical Health Screening.

Data on musculoskeletal symptoms is assessed by means of the Dutch Musculoskeletal Questionnaire (DMQ) [32,33]. In this study, the workers are asked about their symptoms during the last three months and during the past seven days. To provide similarity between the scales, the scale of the seven days period has been adjusted to the two-point scale (yes/no) of the three months.

#### Psychosocial workload

The psychosocial workload is measured by the Dutch version of the Job Content Questionnaire [34,35]. Two constructs of the psychosocial workload (supervisor support and co-worker support) are selected to be measured. These scales have shown moderate to good reliability (0.65-0.81) [36].

#### Awareness, attitude, self-efficacy and social norms

Awareness, attitude, self-efficacy and social norms about reducing physical workload, improving recovery and increasing influence at the worksite are measured to provide insight into the working mechanism of the worksite intervention. Questions about these determinants are formulated based on a structure of questions often used in the health promotion research [37,38].

#### Work engagement

Work engagement is measured with the 12-item questionnaire Utrecht Work Engagement Scale [39]. This scale consists of three dimensions: vigor, dedication and absorption. The psychometric qualities of this scale have been proven to be good [40].

#### The ability and motivation to continue working until the retirement age

Questions about working until the retirement age are assessed by four questions based on the Netherlands Working Conditions Survey [41]. The workers are asked until which age they think they are able and motivated to work. Additionally, they are asked if (physically or mentally) less heavy work can contribute to continue their working life until the age of 65.

### Other variables

#### Sociodemographic and anthropometric data

At baseline, sociodemographic data such as gender, age, level of highest education, working hours per week and anthropometric data such as body height and body weight are assessed.

### Process evaluation

Besides the effect evaluation, a process evaluation is conducted based on the six aspects of Steckler and Linnan (2002): context (organizational and environmental characteristics that affect the intervention), recruitment (sources and procedures used to recruit companies and construction workers), reach (attendance rates of construction workers), dose delivered (the amount of intervention components actually delivered by the trainers), dose received (the extent to which employees use materials or components recommended by the program) and fidelity (the extent to which the intervention was delivered as planned) [42]. In addition, satisfaction (the extent to which the workers were satisfied with the program) is measured. Three of these aspects (context, recruitment and reach) are evaluated by data that is collected in logs since the start of the project in January 2008. Dose delivered and dose received are assessed by checklists completed by the trainers. The remaining aspects, namely fidelity and satisfaction, are obtained by (1) logs from the trainers, (2) questionnaires at three and six months after the start of the intervention, and (3) interviews with supervisors and employees.

### Economic evaluation

An economic evaluation will be conducted alongside the trial and include a cost-benefit analysis and a cost-effectiveness analysis. Both analyses will be performed from a company perspective. The time horizon is 12 months, similar to the trial. A cost-benefit analysis will be carried out to compare the intervention costs with the monetary benefits due to productivity loss. A cost-effectiveness analysis will be conducted for the primary outcomes measures (work ability and health-related quality of life). In the cost-effectiveness analyses, all costs (i.e. costs of the intervention and costs due to productivity loss) will be included and will be compared to the effect on health-related quality of life and work ability. Intervention costs include costs for the development of the intervention as well as the implementation of the intervention (e.g., costs of trainings, video, working hours). Productivity loss (i.e. sick leave and productivity) will be measured with the productivity and disease questionnaire (PRODISQ) [44] and the World Health Organization Health and Work Performance Questionnaire (HPQ) [[45], 46].

### Statistical analyses

Analyses regarding the effectiveness of the primary outcomes and secondary outcomes will be performed after three and six months (short term) and twelve months (long term) by means of multilevel analyses. Multilevel analyses take clustering of observations of workers within the same department into account, as well as repeated measurements within one worker [43]. Due to randomization at the department level, the data will be analyzed at three levels: (1) time, (2) worker and (3) department. Both crude and adjusted linear and logistic regression analyses will be performed. The multilevel analyses using the follow-up measurement (i.e. 3 months) as dependent variable will be adjusted for possible confounding factors such as education and working hours. These variables will also be checked for effect modification. The effect of the intervention at six months and twelve months will be analyzed using all three follow-up measurements (i.e. 3, 6 and 12 months) and will also be adjusted for possible confounders [44]. Effect modification will also be checked again.

For the cost-benefit analysis, the difference in mean intervention costs between the two study groups will be compared to the difference in mean benefits due to sick leave reduction between the two study groups using bias-corrected and accelerated bootstrapping. Confidence intervals (95%) will then be obtained. For the cost-effectiveness analysis, the difference in mean costs (i.e., intervention costs and reduced benefits due to sick leave) between the two study groups will be compared to the difference in mean effects between the two study groups. Cost-effectiveness ratios will be calculated by dividing the difference between the mean total costs between the two study groups by the difference in the mean effects between the study groups. Confidence intervals (95%) will again be obtained by bias corrected and accelerated bootstrapping. For both outcome measures (i.e. health-related quality of life and work ability), cost-effectiveness ratios will be plotted on a cost-effectiveness plane. Acceptability curves will be calculated, showing the probability that the guideline is cost-effective at a specific ratio. Furthermore, sensitivity analyses will be performed to assess the robustness of the results.

All statistical analyses will be performed according to an intention-to-treat principle. In addition, protocol analyses will be conducted for those groups that actually completed the intervention protocol.

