## Methods

### Study design

A Randomized Controlled Trial is performed in order to evaluate the effectiveness of the intervention. This trial is carried out to evaluate whether the worksite prevention program for construction workers improves construction workers' work ability and their health-related quality of life. Construction workers at the worksites allocated to the intervention group receive the worksite prevention program during six months; those allocated to the control group receive no intervention (i.e. usual care). Participants are followed for one year. Primary and secondary outcomes are measured at baseline, and 3, 6 and 12 months after baseline measurement. The study protocol was approved by The Medical Ethics Committee of the VU University Medical Center (Amsterdam, The Netherlands).

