### Randomization

Cluster randomization took place at the level of department within each company. In order to avoid intervention group contamination, to accommodate a potential work-related intervention, to obtain maximal cooperation of employers and employees, and to enhance participants' compliance, cluster randomization was considered the best randomization strategy for this study. The randomization was performed by a research assistant who had no prior information about the departments. For practical reasons, randomization was performed before the baseline measurements. Because the intervention takes place at the worksite, the participants, their supervisors and the trainers cannot be blinded to the group assignment.

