### Sample Size

The sample size was calculated according to the number of cases needed to identify an effect on health-related quality of life. Because the outcome measure SF-12 has rarely been used in intervention studies among the general population, the SF-36 [18,19] was used for the sample size calculation. Calculated effect sizes range (Cohen's D [20]) from 0.58 (which can be considered 'medium' according to effect size conventions) to 0.96 (considered large) [18,21]. Because of the cluster randomization design, a certain loss of efficiency associated with cluster randomization relative to individual randomization was taken into account [22]. An effect size of 0.40 was considered to be the lower boundary of a 'medium' effect size [20]. This effect size can be detected with a power (1-β) of 0.80 and a two-tailed alpha of 0.05 with two groups of 100. Taking a loss to follow up of about 10% into account, we need to recruit a total of 220 participants.

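### The outcome models are built on follow-up values, and the baseline value of the outcome is not named as a covariate although it is measured

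*Protocol article*

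**What the plan says.** The Study design section of the protocol article states: "Primary and secondary outcomes are measured at baseline, and 3, 6 and 12 months after baseline measurement". A baseline score is therefore planned for every outcome.

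The Statistical analyses section describes a multilevel model with time, worker and department as levels, and adds: "Both crude and adjusted linear and logistic regression analyses will be performed". The short-term model is given as "The multilevel analyses using the follow-up measurement (i.e. 3 months) as dependent variable", and it "will be adjusted for possible confounding factors such as education and working hours". The effect at six and twelve months "will be analyzed using all three follow-up measurements (i.e. 3, 6 and 12 months) and will also be adjusted for possible confounders". The section does not say whether the crude or the adjusted result is the primary one.

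On allocation, the Randomization section says: "Cluster randomization took place at the level of department within each company". It also says: "For practical reasons, randomization was performed before the baseline measurements". Participants, supervisors and trainers know the assignment.

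**The concern.** The baseline score can enter an analysis of follow-up data in three usual ways: as a covariate, as one of the repeated responses, or through a change score. The Statistical analyses section describes the response and gives examples of adjusters, and none of the three appears. The two examples named, education and working hours, would normally predict follow-up work ability or SF-12 less well than the baseline value of the same score.

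Two things are at stake. One is precision, because variation between workers that the baseline score could explain stays in the residual. The other is the estimate itself: in an unadjusted comparison of follow-up values, any baseline difference between arms carries through in proportion to the baseline-to-follow-up correlation. Cluster allocation makes larger chance differences possible. Unblinded allocation before baseline measurement also makes it harder to assume that the participants in the two arms are comparable.

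**Working it through.** **Inputs from the article.** Target effect: "An effect size of 0.40 was considered to be the lower boundary of a 'medium' effect size". Power is 0.80, two-sided alpha 0.05, 100 per group, about 10% loss to follow-up, 220 in total (Sample Size).

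**Inputs not in the article.** The baseline-to-follow-up correlation r, the intracluster correlation (ICC), the number and size of departments, and the department-level baseline correlation. The values below are assumptions shown over a range.

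**Step 1, the plan's own figure.** On a standardised scale (SD = 1), n per group = 2 × (1.96 + 0.84)² / 0.40² = 98.1, so 99; the t-based value is 100. Power with 100 per group is 0.807 (t-based 0.804). Allowing for loss, 198 / 0.90 = 220. The stated figures reproduce, with no baseline covariate in the calculation.

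**Step 2, precision.** For a linear outcome, residual variance after adjustment is (1 − r²) times the unadjusted variance. With 100 analysed per group, individual randomisation and d = 0.40:

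| assumed r | 1 − r² | power |
|---|---|---|
| none used | 1.00 | 0.807 |
| 0.3 | 0.91 | 0.843 |
| 0.5 | 0.75 | 0.904 |
| 0.7 | 0.51 | 0.977 |

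These power values illustrate the individual-level case and are not the power of this trial. They do not carry over to the logistic models.

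**Step 3, effect of a baseline difference.** With equal SDs, the shift in an unadjusted follow-up contrast is r × (baseline difference). For a difference of 0.20 SD:
- r = 0.3: 0.3 × 0.20 = 0.06 SD; 0.06 / 0.40 = 15% of the target
- r = 0.5: 0.5 × 0.20 = 0.10 SD; 25%
- r = 0.7: 0.7 × 0.20 = 0.14 SD; 35%

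**Step 4, is 0.20 SD plausible by chance?** The 95% chance range of the baseline difference is ±1.96 × √(2 × DE / 100), where DE = 1 + (m − 1) × ICC and m is the number of workers per department.
- Individual randomisation, DE = 1: ±0.28 SD
- Assumed m = 10, ICC = 0.05, DE = 1.45: ±0.33 SD
- Assumed m = 20, ICC = 0.05, DE = 1.95: ±0.39 SD

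A difference of 0.20 SD lies inside all three ranges, and clustering widens the range.

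**The case against.** The strongest objection is that the covariate list is open. The wording is illustrative, a journal article condenses the full plan, and no statistical analysis plan is shown. This stands in part: the adjusted model may well include the baseline score. A reader might infer that the adjusted analysis leaves it out, but the text does not support that. What remains is that the crude model as written has no baseline value, and that the text offers two weaker covariates as examples without the obvious one.

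Other stronger readings are tempting and should also be resisted:
- *That the estimate is biased.* Under sound randomisation a chance baseline difference is error in one realisation, already reflected in the standard error. Systematic imbalance would need participation to differ by arm, which the article does not report. It places baseline measurement after allocation but does not say when workers were informed or gave consent relative to allocation.
- *That few departments are randomised.* The article gives six companies but no number of departments.
- *That the power calculation ignores clustering.* The Sample Size section says an efficiency loss was allowed for. Choosing 0.40 when the cited effects start at 0.58 may be that allowance, since (0.58 / 0.40)² = 2.1. The allowance is not quantified, but the text does not say that it is absent.
- *That adjustment is worth a stated number of extra participants.* 1 / (1 − r²) is an individual-randomisation formula. Adding workers to the same departments is not equivalent to reducing residual variance in a three-level model.
- *That confounders will be picked from the data.* No selection procedure is described.

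**Conclusion.** The point holds as an improvement at almost no cost, not as an error or a contradiction in the plan. No sentence brings the baseline outcome into an effectiveness model, although it is planned for all primary and secondary outcomes, and naming it is better than what is written.

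The size depends on r. Over an assumed range of 0.3 to 0.7, adjustment removes 9% to 49% of the residual variance in a linear individual-level model. Over the same range, it deals with a shift of 15% to 35% of the target effect if the arms differ by 0.20 SD at baseline. At the low end the benefit is modest. In the clustered design it also depends on the ICC, the department size and the department-level correlation, none of which is given, so no figure for this trial can be stated.

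**What to change.** Add one sentence to the Statistical analyses section. For each outcome, the primary multilevel model, both at 3 months and over 3, 6 and 12 months, includes group, the baseline value of that same outcome and a prespecified covariate list (for example education and working hours). The crude model is reported as supportive.

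The cost is that sentence and a short rule for workers without a baseline score, such as mean imputation of that covariate. No additional measurement, visit or participant is needed.

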## Discussion

This paper presents the design of a randomized controlled trial to investigate the effectiveness of a multi-component worksite prevention program. The content of the intervention consist of two preventive training sessions of a physical therapist, a Rest-Break tool, and two empowerment training sessions.

To our knowledge, this is the first study that will evaluate a multi-component intervention in the construction industry that targets both the individual capacities as well as the work environment. As work ability is a multidimensional concept, such a worksite prevention program seems potentially effective in improving the work ability. Moreover, outcome measures (e.g., work ability, health-related quality of life) will be evaluated which might predict a healthier working life among construction workers.

A strength of the current study is that the evaluation of the intervention will not only give insight into the (cost-)effectiveness, but also into the process of the intervention. The process evaluation aims to describe (1) the reach of the program, (2) the initial expectations and satisfaction of the participating construction workers and (3) the intention of participating companies to further implement the intervention program in the future. Due to time limitations, process evaluations are infrequently conducted in the field of worksite prevention or health promotion and are rarely compared to the outcomes of the study [42,45]. Results of the process evaluation are very relevant as they may provide insight into the working mechanisms of the intervention, and into process factors influencing the outcomes, e.g., was the program intended as planned, and what was the satisfaction with the different components. Moreover, and even more important, the process evaluation will provide information to improve implementation of the program in the future.

A limitation of the current study is that intervention consists of several components and that the RCT is two-armed (control versus intervention), which does not allow separate evaluation of each component of the intervention. As a consequence, eventual effectiveness of the program can only be attributed to the entire program. However, the process evaluation will focus on the entire program as well as on the separate components and will therefore qualitatively gain insight into the working mechanisms of the different components of the intervention.

This intervention may benefit workers as well as employers. If the intervention proves to be effective, the construction worker will benefit from this by an improved health and a healthier working environment and, as such, will contribute to the prolongation of their working life. As a consequence, employers may benefit from having healthier workers in terms of a reduced sick leave and a higher productivity. If this program proves to be cost-effective, the protocol will be made available to all companies in the construction industry as well as for companies in other sectors with high physical work demands.
